### Concealment mechanism {16b}

Study participants are randomized into control and intervention groups after signing consent and completing the baseline survey. Research recruiters and subjects do not know the intervention assignment until the subject is randomized in REDCap.

### Implementation {16c}

The project manager generated the allocation sequences and uploaded them to the Randomization Module in REDCap. The research study team involved in recruitment will screen and enroll subjects into the study and assign them to intervention groups by using the randomize button within REDCap, which only reveals the intervention group for the current participant. The clinical care team will determine the method of care required for the patient to confirm if the subject will qualify for daily dressing changes. These decisions will be made based on treatment needs without research influence.

## Assignment of interventions: blinding

### Who will be blinded {17a}

We cannot blind the participants, caregivers, or research team from the assigned intervention since one group will use the VR headset and one will not. The study biostatistician will be blinded to the intervention group while performing analyses on the primary outcome. The data will be blinded by removing labels such as “VR” and “Control” and will be replaced with unidentifiable letters (i.e., “A” and “B”). The biostatistician will need to become unblinded for secondary outcomes as those in the intervention group will be the only ones answering the VR experience questions.

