#### Secondary outcome measures

Change in self-reported anxiety (Spielberger State-Trait Anxiety Inventory for Children (STAI-CH) score 6 (low anxiety)–24 (high anxiety)). Anxiety is assessed at baseline (recruitment visit) and before each dressing change for about 1 week. The changes in anxiety will also be compared between the intervention and control groups.

Pain medication reduction. The caregiver will report pain medication usage (name and dosage) for about 1 week after each dressing change. The pain medication used will be compared between the intervention and control groups.

Average self-reported VR experience (NRS 0 (min)–10 (max) for the degree of realism, pleasure, and satisfaction with VR). For about 1 week, these VR experience questions are assessed at each dressing change for those in the intervention group.

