### Procedure for unblinding if needed {17b}

The biostatistician will be unblinded for full analyses by providing the full dataset with complete data labels and VR questions. This unblinding will occur after the primary outcome analysis has been completed.

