#### Child surveys (self-reported)

All participants (control and intervention group) will self-report anxiety prior to the dressing change using the STAI-CH scale with ratings from not at all to very much. After the dressing change is completed, the child will answer the remaining survey questions assessing overall pain score (NRS, 0–10), worst pain score (NRS, 0–10), and time spent thinking about pain (NRS, 0–10). The survey is completed once daily alongside dressing changes for 7 days until the patient returns for their follow-up appointment. Survey questions remain the same for each daily dressing change.

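### The biostatistician is unblinded for all secondary outcomes for a reason that fits only the VR-only items; pain medication, and anxiety as classed secondary, could stay under the A/B codes

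*Protocol article*

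**What the plan says.** All statements are in the protocol article.

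- **Scope of the blind.** Who will be blinded {17a} explains that participants, caregivers and the research team cannot be masked. For the analyst it says: "The study biostatistician will be blinded to the intervention group while performing analyses on the primary outcome". The mask consists of replacing the arm labels with letters.
- **Reason for ending it.** The same section continues: "The biostatistician will need to become unblinded for secondary outcomes as those in the intervention group will be the only ones answering the VR experience" items. No other reason is given.
- **Timing and content of the release.** Procedure for unblinding if needed {17b} says: "The biostatistician will be unblinded for full analyses by providing the full dataset with complete data labels and VR questions". It adds: "This unblinding will occur after the primary outcome analysis has been completed". There is one release, and it carries the labels and the VR items together.
- **Secondary outcomes.** Secondary outcome measures lists three: anxiety, pain medication and VR experience. On anxiety: "The changes in anxiety will also be compared between the intervention and control groups". On medication: "The pain medication used will be compared between the intervention and control groups". VR experience is collected in the intervention group only.

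**The concern.** The rule is wider than its reason. Questions that only one arm answers would reveal which letter is which, so the analyst cannot see them and stay masked. That justifies withholding those questions until later. It does not justify showing arm labels for outcomes that both arms report on the same items.

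The biostatistician's mask is the only one the article describes. Where it is dropped, any decision made during analysis is made with the arms known. The clearest place for such decisions is medication. Caregivers write down the product and dose, and these entries must be turned into morphine equivalents before the PIOC score can be built. Opioid reduction is part of Aim 1, and PIOC is the measure named in Hypothesis 1, so these results will carry weight in the trial's conclusions.

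**Working it through.** No sample size, power or error rate enters this point, so there is no figure to reproduce. The check is to sort each analysed item by who supplies the data and by how the article classes it, and then ask whether the stated reason applies.

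| Item | Data from | Class in the article | Does the VR-only reason apply? |
|---|---|---|---|
| Child-reported overall pain | Both arms | Primary (Sample size; Aim 1) | No; already blinded |
| Pain medication | Both arms, same form | Secondary, with no conflicting statement | No |
| Anxiety (STAI-CH) | Both arms | Secondary in Secondary outcome measures; part of the primary outcome in the Abstract | No |
| Child worst pain, caregiver-reported pain | Both arms | Primary in Primary outcome measure; secondary in Aim 1 | No |
| PIOC | Both arms | Not stated; named in Hypothesis 1 and given its own analysis section | No |
| VR experience, Aim 2 scores, caregiver-reported VR use, VR-related adverse effects | VR arm only | Secondary, Aim 2 or safety | Yes |

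**Data source.** For anxiety, Child surveys says: "All participants (control and intervention group) will self-report anxiety prior to the dressing change". For medication and caregiver-rated pain, VR-PAT guardian surveys says that the VR arm completes the same items as the control arm, with VR questions added.

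**What the methods need.** The article's between-arm methods are t-tests, chi-squared tests, a linear mixed model, ranks pooled over both arms and a Mann–Whitney *U* test. Each needs a variable with two levels. None needs to know which level is VR. The A/B coding already planned for the primary analysis is therefore enough.

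**Count.** Of the three listed secondary outcomes, the reason fits one (VR experience). The other two (anxiety and medication) are two-arm comparisons. Medication is exposed on any reading of the article. Anxiety is exposed if Secondary outcome measures governs rather than the Abstract.

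**Volume of medication data.** Table 1 gives seven medication questionnaires per child, so at most 200 × 7 = 1,400 forms. This is a ceiling: the plan assumes 10% dropout, eligibility requires daily changes for only about 5 days, and forms without medication need no coding. It indicates workload and does not measure bias.

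**The case against.** Several objections are sound and limit the point.

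- **Classification.** A reader might infer that anxiety, worst pain, caregiver-reported pain and PIOC are all certain to be analysed with labels visible. The article does not support that. The Abstract puts anxiety in the primary outcome, Primary outcome measure includes worst and caregiver-reported pain, and PIOC is given no status. On those statements some of these outcomes would keep the blind. Only medication is classed as secondary without conflict.
- **Covariate choice.** It is tempting to cite the mixed model, whose covariates are chosen after looking at imbalance, as discretion in the exposed outcomes. That model's dependent variable is child-reported overall pain, which is the primary variable, so it can be read as falling under the blind.
- **Who codes medication.** A reader might assume that the biostatistician does. The article does not say. Data management has research staff enter the data and a team member or PI verify them, and the research team is unblinded. If staff do the conversion, a longer blind for the biostatistician alone would not protect it.
- **Room for judgement.** Anxiety and pain are simple scale scores. The article names the t-test for the pain scores and fixes the AUC rule, ranking and rank test for PIOC. Together with the intention-to-treat principle, this limits analyst choice, so the blind is not the only safeguard.
- **Main source of bias.** Children and caregivers report their own outcomes knowing the arm. No change to the analyst's blind alters that.

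What remains is that the stated reason does not support the stated rule. For medication at least, the blind is given up with nothing gained.

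**Conclusion.** The point holds in a limited form. Sections {17a} and {17b} end the blind for every secondary outcome on grounds that apply only to VR-only items. Pain medication loses the blind without need, and so does anxiety as classed under Secondary outcome measures. Worst pain and caregiver-reported pain follow if the Aim 1 section governs. PIOC follows unless it is treated as part of the primary analysis.

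The size is modest. The primary t-tests are blinded as planned, and no stated result becomes invalid. What is gained is protection against analyst choices, mainly in medication coding and the secondary analyses. The change is worth making because it costs almost nothing and can be settled before analysis, since the article describes recruitment as ongoing.

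The conclusion assumes that the two blinding sections state the operating rule, and that the VR-only fields can be separated from the shared fields. The separate VR question sets described under Data collection suggest that they can.

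**What to change.** 1. Reword {17a} and {17b} so that A/B coding stays in place until every between-arm analysis is complete and locked: overall, worst and caregiver-reported pain, anxiety, medication and PIOC, with their subgroup and imputation analyses. A rule that names every two-arm comparison works whichever outcome classification is finally adopted.
2. Split the data release. The first release holds the shared items under A/B codes, with VR-only fields and free-text caregiver comments withheld, since comments may reveal the arm. The second holds labels and VR-only fields, for VR experience, Aim 2, VR use and VR-related adverse effects.
3. State who converts medication entries to morphine equivalents. That person should work from a listing without arm labels or VR items, and the listing should be locked before labels are released.
4. Reconcile the status of anxiety, worst pain, caregiver-reported pain and PIOC across the Abstract, Outcomes and Aim 1 sections, so that the scope of the blind is unambiguous.

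The cost is revised wording and a two-step release prepared by someone other than the biostatistician. Data management already gives the study coordinator and the contact PI access to the full dataset, so no new role, data or participants are needed.

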### Procedure for unblinding if needed {17b}

The biostatistician will be unblinded for full analyses by providing the full dataset with complete data labels and VR questions. This unblinding will occur after the primary outcome analysis has been completed.

## Data collection and management

### Plans for assessment and collection of outcomes {18a}

#### Content and protocol for the control group

Participants in the control group are given a folder of daily surveys and instructed to complete their standard wound care as instructed by their care team. Then, they complete the provided daily surveys for both the child and caregiver, indicating the date and dressing change number for each day.

#### Child surveys (self-reported)

All participants (control and intervention group) will self-report anxiety prior to the dressing change using the STAI-CH scale with ratings from not at all to very much. After the dressing change is completed, the child will answer the remaining survey questions assessing overall pain score (NRS, 0–10), worst pain score (NRS, 0–10), and time spent thinking about pain (NRS, 0–10). The survey is completed once daily alongside dressing changes for 7 days until the patient returns for their follow-up appointment. Survey questions remain the same for each daily dressing change.

#### Guardian surveys (proxy report)

Caregivers (control and intervention group) of the participating child conducting the dressing change are asked to report their observation of the child’s pain after wound care (NRS, 0–10). Caregivers are also asked to document any opioid or pain medication given (name, brand, and dose) and are given the opportunity to share anything of note for that dressing change. The survey remains the same for each day of wound care and is to be completed once daily after the child surveys.

#### Content and protocol for the intervention (VR) group

Participants in the intervention (VR-PAT) group are given a folder similar to the control group with daily surveys, with the addition of download instructions for the VR-PAT smartphone application and a VR headset best suited for the participating child. The child is asked to wear and play the approved VR game during the dressing change, and then both the child and caregiver are instructed to complete the daily surveys after wound care.

#### VR-PAT child surveys (self-reported)

In addition to self-reporting anxiety STAI-CH survey questions prior to wound care and assessing their overall pain score (NRS, 0–10), children are asked about their experience with the VR game (degree of realism, fun, engagement, and satisfaction) and pain perception while playing the VR game (NRS, 0–10). Participants are also asked to report any simulator sickness associated with the VR game.

#### VR-PAT guardian surveys (proxy report)

Primary caregivers will complete the same pain assessment (NRS, 0–10) and medication documentation as the control group, with the addition of questions regarding the VR-PAT use. Caregivers will note the amount of time the child played, willingness to participate, number of wound care interruptions, ease of use, and helpfulness of the device. If any other details about the dressing change would like to be shared, a comment section is provided for notes.

### Plans to promote participant retention and complete follow-up {18b}

Based on our pilot study, we do anticipate losing some participants to follow-up. We will attempt to promote retention by emphasizing the importance of returning surveys after their week of home dressing changes at the time of recruitment. The recruiter will also ask the legal guardian for a phone number where they can receive reminder calls. Participants in the VR group will be asked to download the app at the time of recruitment; however, if they choose not to, they may download it at home and are provided with contact information for the research team and receive a check-in phone call on the next business day following recruitment to ensure there were no technological issues. All participants will receive a reminder call before their next clinic appointment (or at the 7-day mark if they are not returning to the clinic). Additional reminder calls will be made once per week for up to 3 weeks to encourage the return of surveys. We will also allow participants to return surveys in person at a clinic appointment, by taking a photo and emailing them to an email address created specifically for this project, or by mailing them in a provided prepaid, self-addressed envelope. Participants who return surveys, thus completing all study procedures, will receive an incentive of $25 on a Greenphire ClinCard.

### Data management {19}

Data from the baseline survey, child and caregiver questionnaires, and follow-up survey will be independently entered and stored electronically in a secure REDCap database hosted on the NCH servers by trained research staff. Only researchers listed on the approved IRB will be granted access. Once data have been collected and entered, another team member or PI will verify the records to ensure the information is complete. Research staff from each site will only have access to participant data within their Data Access Group, except for the study coordinator and the contact PI, who will have access to the full data set. Each research participant is assigned a unique Study ID. The master file that links the participants’ names to their Study IDs will be maintained only in a secure file folder in a password-protected computer at the Research Institute at NCH and Parkland Health. All measurement and randomization procedures will only use Study IDs to record data without participants’ names attached.

Any technical-related beta feedback provided from iPhone users through the TestFlight app will be received via NCH e-mail, and all identifiers will be removed before being saved in a secure file folder on a password-protected computer at the Research Institute at NCH. De-identified technical feedback will be forwarded to the VR developers (listed on the IRB application) to assist with improving the app for future studies.

### Confidentiality {27}

Prior to enrollment, screening spreadsheets and other electronic databases to access patient charts will be kept in a secure file folder on password-protected computers in the Research Institute at NCH and at Parkland Health. Only researchers on the IRB will have access to the secure folder where the file is located.

Eligible subject information will be entered in a locked research office on a hospital-approved password-protected computer. Enrolled subjects will be assigned a study ID number. The PI and limited trained research staff will maintain all components of the research record containing participants’ identifying information.

Hard copies and information collected during study enrollment are kept in a secure locked file cabinet in a locked office, with only study staff having access. Publication will not identify subjects or contain information leading to identification. The study team has no plans to contact the subjects after their study participation or to share PHI with anyone outside the study team.

### Plans for collection, laboratory evaluation, and storage of biological specimens for genetic or molecular analysis in this trial/future use {33}

Not applicable. No biological specimens will be collected.

## Statistical methods

### Statistical methods for primary and secondary outcomes {20a}

#### Aim 1

In the primary analysis, the child-reported overall pain NRS score will be compared between the VR-PAT and control groups during each of the first 7 days of follow-up using a two-sample *t*-test. The *p* values will be adjusted by Bonferroni correction to account for multiple comparisons and then compared to the critical value of 0.05 to determine statistical significance. In the secondary analysis, child-reported worst pain score, parent-observed overall and worst pain scores, child engagement and experience with VR, caregiver report of VR use, and adverse effects related to engagement with VR will be compared between the two study groups using a two-sample *t*-test (for continuous variables) and chi-squared test (for categorical variables). To estimate the overall difference in the child-reported overall pain score between the two study groups over the 7 days of follow-up, a linear mixed effect model with random intercept accounting for the correlation among repeated measures of pain scores will be fit. The dependent variable of the model will be child-reported overall pain score. The independent variables of the model will contain the study group, time (follow-up days), and any potential confounders deemed unbalanced between the study groups. The coefficient of the study group is the estimated overall difference in the pain score. To further explore whether the trend of child-reported overall pain score over the 7 days differs between study groups, the same linear mixed effect model as above will be fit with the addition of interaction between the study group and time. The coefficient of the interaction term estimates the difference in the trend of pain scores over time.

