### Eligibility criteria {10}

Eligibility will be assessed using the following criteria: (a) undergoing treatment for acute burn injury; (b) age 6–17 years, inclusive; (c) receiving their first outpatient clinic dressing change or being discharged from the ED or inpatient burn unit; (d) having a dressing that requires daily changes at home for about 5 days after their first outpatient appointment or discharge from the hospital; (e) patient and family caregivers can communicate (read and write) using English or Spanish; and (f) report an NRS pain score of ≥ 1 (NRS 0–10 with 10 being worst pain) from the most recent dressing change. To minimize the possibility of confounding variables, the following exclusion criteria will be applied: (a) any wounds that may interfere with study procedures (i.e., face burns); (b) vision, hearing, or cognitive/motor impairments preventing valid administration of study measures; (c) history of motion sickness, seizure disorder, dizziness, or migraine headaches precipitated by visual auras; (d) minors in foster care, prisoners, or those who are currently pregnant; (e) suspected child abuse; (f) unable to communicate in English or Spanish; and (g) families who do not have access to a VR compatible smartphone.

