## Assignment of interventions: allocation

### Sequence generation {16a}

A random-block randomization scheme with a block size of four will allocate participants to either intervention or control at a 1:1 ratio without stratification. Each site had its own randomization scheme stored in its respective Data Access Group in REDCap to ensure that subjects within each arm were distributed evenly between each site.

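### The primary daily t-tests leave out the pre-randomisation pain score and site, and the supplementary mixed model chooses its covariates by observed imbalance: a loss of precision, not of validity

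*Protocol article*

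**What the plan says.** All references are to the protocol article.

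- **Primary analysis** (Statistical methods {20a}, Aim 1). The outcome is the overall NRS pain rating given by the child, which "will be compared between the VR-PAT and control groups during each of the first 7 days of follow-up using a two-sample" comparison of means by Student's test. No covariate is named. On multiplicity, the plan says of the resulting p values that these "values will be adjusted by Bonferroni correction to account for multiple comparisons and then compared to the critical value of 0.05".
- **Mixed model** (same section). Its purpose is given as "To estimate the overall difference in the child-reported overall pain score between the two study groups over the 7 days of follow-up". The plan for this purpose is that "a linear mixed effect model with random intercept accounting for the correlation among repeated measures of pain scores will be fit". It contains group, time and "any potential confounders deemed unbalanced between the study groups". A group-by-time interaction is then added as a further exploration. Aim 2 uses random-intercept models for the trends in engagement, fun and realism.
- **Pre-randomisation pain** (Eligibility criteria {10}). A child must report an NRS pain score of at least 1 "from the most recent dressing change". Recruitment {15} says that staff assess pain status at the approach. Children are "randomized into control and intervention groups after signing consent and completing the baseline survey" (Concealment mechanism {16b}), so the score precedes allocation.
- **Site** (Sequence generation {16a}). "Each site had its own randomization scheme stored in its respective Data Access Group in REDCap", with blocks of four. The section also says there is no stratification, but a separate blocked list per site is stratification by site in effect.

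**The concern.** A pain score on the outcome's own 0–10 scale, taken before randomisation, is usually among the better predictors of later pain. The primary tests do not use it. They also ignore the factor within which the allocation was blocked. Both omissions leave explainable variance in the error term and widen each daily interval.

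The mixed model has a different problem. Its covariates depend on which variables look unbalanced once the data are in. The protocol gives neither a list nor a criterion, and the rule omits a strong predictor whenever it happens to balance. This is a stated rule rather than a detail left open, so an analysis plan that named its covariates in advance would have to depart from it.

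A smaller point is that a random intercept alone assumes all children share the same slope within a group. If slopes differ, the standard error of the group-by-time term, and of the Aim 2 time trends, is too small.

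**Working it through.** **Inputs from the protocol** (Sample size {14}): 89 evaluable per group, 80% power, two-sided 0.01 per day, 10% dropout. Neither the control mean nor the SD is given.

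**Inputs assumed:** correlation r between pre-randomisation NRS and daily pain, 0.2 to 0.6; difference between site means, 0.2 to 0.5 within-site SD; slope and residual SDs as stated in step 5.

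**1. The plan's own figure.** The 89 cannot be rebuilt without a mean and SD. Solved backwards with the noncentral t, 89 per group at 80% power and 0.01 implies d = 0.517. Dropout reproduces: 89/0.9 = 98.9, so 99.

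**2. Per-day power without covariates.** Seven tests under Bonferroni are each judged at 0.05/7 = 0.00714. With d = 0.517 and 89 per arm, power is 80.0% at 0.01 and 76.6% at 0.00714.

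**3. Adjusting for pre-randomisation NRS.** The residual SD is multiplied by √(1 − r²), so the effective difference is 0.517/√(1 − r²).

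| r (assumed) | Variance removed, r² | Effective d | Power at 0.05/7 | Power at 0.01 |
|---|---|---|---|---|
| 0 | 0% | 0.517 | 77% | 80% |
| 0.2 | 4% | 0.528 | 79% | 82% |
| 0.3 | 9% | 0.542 | 81% | 84% |
| 0.5 | 25% | 0.597 | 89% | 91% |
| 0.6 | 36% | 0.646 | 94% | 96% |

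**4. Adjusting for site.** Take two equal sites whose means differ by s within-site SDs, and set the total SD to 1. The within-site SD is then f = 1/√(1 + s²/4). With SE = √(2/89) = 0.150, d/SE = 3.45 and z = 2.69 at 0.05/7, the normal approximation gives:
- unadjusted power = Φ((3.45 − 2.69)/f);
- adjusted power = Φ(3.45/f − 2.69).

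For s = 0.2, 0.3 and 0.5 this is 77.7% against 78.1%, 77.9% against 78.8%, and 78.3% against 80.7%. The gain is about 1 point or less up to s = 0.3, and about 2 points at s = 0.5. Ignoring site makes the test slightly conservative: at nominal 0.01 the true level is 0.0096 to 0.0079.

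**5. Random intercept only.** For seven equally spaced days the sum of squares about the mean day is 28. With slope SD τ and residual SD σ, the true variance of a child's fitted slope is τ² + σ²/28. The random-intercept model reports (σ² + 28τ²/6)/28. With σ = 1.5 and τ = 0.1, 0.2 or 0.3 NRS per day, true against reported is 0.0904 against 0.0820, 0.1204 against 0.0870, and 0.1704 against 0.0954. A nominal 5% test then has a type I error of about 6%, 10% or 14%.

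**6. What selection by imbalance recovers.** As an illustration, one day was simulated at 0.01 with 89 per arm (20,000 runs), adjusting only when baseline pain differed at p < 0.05. That threshold is assumed. Power for no adjustment, adjustment when unbalanced and adjustment always was 80/80/84% at r = 0.3, 80/81/91% at r = 0.5 and 80/81/95% at r = 0.6. Selection recovers almost none of the gain.

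**The case against.** **The primary analysis is sound.** A two-sample t-test on a randomised outcome is unbiased, Bonferroni controls the family-wise error, and the sample size was planned for this test. That stands.

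**The gain is not established.** The protocol gives no correlation. The score is a single screening report, restricted to 1 or more and often from a clinic rather than a home dressing change, which may weaken its correlation with home pain. The protocol does not say that it is kept for analysis. All of this stands. It is why the range starts at r = 0.2, where the gain is about 2 points.

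**Analyst choice does not reach the primary result.** A reader might infer that the imbalance clause compromises the main finding. It does not: the t-tests contain no covariates, and under Who will be blinded {17a} the biostatistician works with coded arms for the primary outcome. Only the mixed model is affected.

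**Replacing the primary test.** A reader might also infer that one week-average contrast should replace the daily tests, since per-day power is 77% and the week-average test would exceed 95%. That comparison is not like with like, because the plan aims to detect a reduction on any of the seven days. With d = 0.517 on every day and within-child correlation 0.4 to 0.8 (assumed; 20,000 simulated trials), any-day Bonferroni power is 99% to 93%, against 99.8% to 96% for the week average. If the effect fades linearly to zero by day 7, the figures are 87% to 80% against 69% to 47%. The choice between them is a design decision, not an error.

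**The slope issue is peripheral.** It concerns an exploratory interaction and descriptive Aim 2 trends, and its size rests on assumed SDs. That stands, so it is a minor point.

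**Conclusion.** The point holds as a matter of precision and prespecification. The primary comparisons leave out a predictor obtained before randomisation from every eligible child, and the factor used to block the allocation. At the implied d of 0.517 with 89 per arm, the pre-randomisation score is worth 2 to 17 points of per-day power at 0.05/7 (77% to between 79% and 94%), depending on a correlation of 0.2 to 0.6 that the protocol does not supply. Site is the minor part, and including it mainly makes the analysis match the allocation.

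The imbalance rule is a real weakness, confined to the mixed model. The documents do not support calling the t-tests invalid or biased, or requiring a different primary estimand. The change is worth making before database lock, but the trial's conclusions do not depend on it.

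**What to change.** 1. Keep the seven Bonferroni-adjusted daily comparisons as primary. Run each as an ANCOVA of that day's child-reported overall NRS on group, pre-randomisation NRS and site.
2. In the mixed model, delete the clause that admits covariates by imbalance. Enter pre-randomisation NRS and site as fixed covariates, named in advance.
3. Minor: add a random slope for time to the exploratory group-by-time model and to the Aim 2 trend models.
4. Confirm that the NRS score used for eligibility is recorded as an analysis variable for every randomised child, including those already enrolled.

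The cost is a wording amendment, dated before database lock and before outcome data are examined by arm. Two covariates cost two degrees of freedom out of about 176 (2 × 89 − 2), which is negligible. If the screening score is on file, no new data are needed and the planned sample size can stay as it is. If it was not kept for some children, that has to be known before the covariate is fixed.
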